## Abstract

**Background:**

Stigma and discrimination are a significant public health concern and cause great distress to people with mental illness. Healthcare professionals have been identified as one source of this discrimination. In this article we describe the protocol of an international, multisite controlled study, evaluating the effectiveness of READ, an anti-stigma training for medical students towards patients with mental illness. READ aims to improve students’ ability to minimise perceived discriminatory behaviours and increase opportunities for patients, therefore developing the ability of future doctors to address and challenge mental illness related discrimination. READ includes components that medical education research has shown to be effective at improving attitudes, beliefs and understanding.

**Methods/design:**

READ training was developed using evidence based components associated with changes in stigma related outcomes. The study will take place in multiple international medical schools across high, middle and low income countries forming part of the INDIGO group network, with 25 sites in total. Students will be invited to participate via email from the lead researcher at each site during their psychiatry placement, and will be allocated to an intervention or a control arm according to their local teaching group at each site. READ training will be delivered solely to the intervention arm. Standardised measures will be used to assess students’ knowledge, attitudes and skills regarding discrimination in both the intervention and control groups, at baseline and at follow up immediately after the intervention. Statistical analyses of individual-level data will be conducted using random effects models accounting for clustering within sites to investigate changes in mean or percentages of each outcome, at baseline and immediately after the intervention.

**Discussion:**

This is the first international study across high, middle and low income countries, which will evaluate the effectiveness of training for medical students to respond effectively to patients’ experiences and anticipation of discrimination. The results will promote implementation of manualised training that will help future doctors to reduce the impact of mental illness related discrimination on their patients. Limitations of the study are also discussed.

## Background

Mental health related stigma and discrimination constitute a significant public health concern, leading to reduced help seeking and access to healthcare [1, 2], fewer opportunities for education and work [3, 4], and increased co-morbidity [5] and mortality [6, 7] for people with mental illness. There is a need for interventions to address this discrimination as acknowledged by international mental health policies [8, 9]. For instance in the UK mental health policy for 2011–2015 [8], one of the six key objectives of the Government’s mental health strategy specifies the need to ensure fewer people experience stigma and discrimination due to their mental illness. Internationally, the World Health Organisations’ Mental Health Action Plan 2013–2020 [9] stipulates that people affected by mental illness should be able to participate fully in society and at work, free from stigmatisation and discrimination.

Several professional groups have been identified as significant sources of stigma and discrimination. One such group is healthcare staff, including doctors and medical students [10]. As a result, health professionals have been identified as a target group by two national anti-stigma campaigns: Opening Minds in Canada [11] and One of Us in Denmark (http://www.en-af-os.dk/da/Om%20kampagnen/Fokusomraader.aspx). In addition the Andalusian Strategy Against Stigma campaign in Spain developed an action plan with several interventions for health professionals, including training courses and a video documentary (http://www.1decada4.es/course/view.php?id=12#profesionales). However, the potential for doctors to show leadership in reducing the impact of discrimination has not yet been thoroughly examined [12]. Any training on mental health related stigma and discrimination should therefore acknowledge doctors’ roles as both sources of discrimination and as potential anti-stigma change agents. To date, medical student education has done only the former [13, 14], with previous training showing short term changes in attitudes but with no focus on future anti-stigma agency in either content or assessment. Further, these projects have not made use of research in medical education for students, which has highlighted the effectiveness of critical reflection and self reflection as methods to improve attitudes, beliefs, understanding of a subject and satisfaction in learning. A number of reflective techniques used in healthcare education have been associated with these improvements, particularly critical reflection [15]. Critical reflection is defined as the emotional and intellectual activity through which people critically assess content, and process information to interpret and give meaning to an experience [16]. Critical reflection is part of a model of learning called reflective practice, which has been frequently used in healthcare education over the last decade [15, 17]. In addition reflection is shown to be positively associated with attitudes, beliefs and understanding [15]. Therefore reflection is an important component to include in any educational training for medical students.

This project implements training for medical students entitled ‘Responding to Experienced and Anticipated Discrimination’ (READ), and aims to evaluate its effectiveness by measuring changes in students’ knowledge, attitudes and skills in responding to mental illness related discrimination.

There are elements from both medical education and anti-stigma interventions to create an intervention tailored to this group, and focussed on behaviour in addition to attitudes and knowledge.

### Development of READ

The aim of READ training is to develop the role of future doctors to address and challenge mental illness related discrimination, by improving medical students’ ability to:increase opportunities for patients e.g. for access to health services or employment (due to patients’ anticipation of discrimination),respond to discrimination and apply current evidence for effective anti-stigma interventionsminimise behaviours that may be experienced by patients as discriminatory.

The content, delivery and evaluation of READ was informed by: (i) studies of patients’ experiences of discrimination;(ii) studies of stigma and discrimination among healthcare professionals; (iii) research on contact-based education to reduce stigma in health care professionals; and (iv) the broader field of study on intergroup contact as a means to reduce prejudice. The decision to use contact based education was based on several reviews of interventions to reduce stigma and prejudice [18–21] including among young people [22] and health professionals [10], supplemented by more recent papers on the evaluation of interventions with health professionals delivered as part of Canada’s anti-stigma programme [23, 24]. The literature on patients’ experiences from which content was derived was based on a systematised search for studies on mental health related discrimination.

Patients’ experiences have been studied using both quantitative and qualitative methods. Surveys using the Discrimination and Stigma Scale (DISC) include examples of experiences provided by [25–27]. Qualitative work on subjective experiences of stigma in patients, relatives and mental health professionals provides richer data on the range of experiences patients find discriminatory [28, 29]. These examples are included in the READ presentation.

Research in both Emergency Department and general hospital settings has identified factors contributing to perceived discrimination and diagnostic overshadowing (when a physical illness is incorrectly attributed to the patient’s diagnosis of mental illness) [30, 31]. These factors and observations of discriminatory practice, witnessed by healthcare staff, are discussed in the training.

Evaluation of contact-based education delivered through the Canadian anti-stigma programme Opening Minds [11] identified the key components associated with positive stigma related outcomes. This study evaluated anti-stigma training programmes for healthcare professionals across Canada, and used qualitative and quantitative analysis to determine the key elements present in the most effective programmes. The results showed that (i) including multiple forms of contact with people with lived experience of mental illness (i.e. live and filmed), and (ii) personal accounts with a focus on recovery, were significantly associated with better outcomes on mental illness related knowledge and attitudes. READ has therefore incorporated both these key components: to include a person with lived experience of mental illness (expert by experience as educator) to co-deliver the training with a psychiatrist, and short films of testimonies by experts by experience, to ensure the training comprises multiple forms of contact. In addition the expert by experience will provide a personal account of her/his illness and recovery process, therefore ensuring the “focus on recovery” component is addressed. Finally, a previous study of anti- stigma training for medical students [14] suggested that a repeat or “booster” session might facilitate sustained improvements in mental illness related knowledge and attitudes. READ includes a first session followed by a second “booster” session, which may consequently contribute to longer term improvement in these outcomes.

READ developed using previous research on intergroup contact (as in this case healthcare professionals are one group and patients with mental illness are another group). A study in the UK [32] assessed the application of intergroup contact theory to mental health related stigma. This work examined the influence of different types of imagined contact with people with schizophrenia, and concluded that imagined contact might increase intergroup anxiety (and therefore desire for social distance) unless it was purposefully structured to reflect a positive imagined contact experience. A meta-analysis of over 500 studies [33] found that reduced anxiety and increased empathy towards the other group are key mediators of the effect of intergroup contact on prejudice. We have taken these mediators into account in both the development and evaluation of READ. It is important to note that this design generally treats the two groups as if they are dichotomous, in this case that the psychiatry trainer and medical students do not have lived experience of mental illness. However, in the second READ session the psychiatrist trainer discusses stigma in relation to the self (internalised stigma) and in relation to colleagues, including as it relates to professionalism and regulatory requirements for doctors to prevent their illness from affecting patient care.

READ delivery began in 2015 in the UK to medical students at two medical schools. These have acted as pilot teaching sites for the training components. The content and structure of the training has been revised for the proposed study, using feedback from focus groups with the participating medical students in the pilot teaching sites. Past and current experts by experience include NHS Trust employees who have accessed mental health services, and peer support workers with a diagnosis of mental illness.

## Methods/design

This is a multisite, non-randomised controlled study. The sites are 25 medical schools in 15 countries, including low, middle and high income countries, as outlined in Table 1 below. Sites were recruited via previous contact within the INDIGO Network (a collaboration of researchers in different countries co-ordinated by the Centre for Global Mental Health, King’s College London) or personal invitation to researchers interested in challenging stigma in healthcare professionals.

**Table 1 Tab1:** Distribution of medical schools

	Continent	Country	Number of sites
	Europe	UK	3
		Czech Republic	1
		France	2
		Spain	3
		Italy	2
		Portugal	3
		Hungary	1
		Turkey	1
	Asia	India	2
		Japan	1
		Taiwan	1
		China	1
	Africa	South Africa	1
		Nigeria	2
		Tunisia	1
Summary	3	15	25

### Intervention

The READ intervention has been manualised to provide guidance on implementation for the sites, which includes suggestions on how to adapt the training to make the content suitable for each site’s resources and culture. The manual also includes a section on preparation and practical considerations to aid with implementing the study. It attempts to address the reduced resources in some of the sites by suggesting that sites in the same country share resources where possible, and if necessary. The sites also have the option to correspond with each other to share strategies to facilitate implementation.

READ training will be provided to students in small groups according to local teaching arrangements. Students will be able to feed back after the role play and to ask questions of the trainers.

The first session is delivered over 1.5 h near the start of the psychiatry rotation in each medical school; the second session, lasting 1 h, takes place later before the end of the rotation. The length of the psychiatry rotation varies in each medical school, however we advised at least 1 week elapses between the two sessions. This will allow time for students to identify examples of discrimination to discuss in the second session. The training is designed to also help the students interact more effectively with patients they meet during the psychiatry rotation. Therefore it is intended to enhance their overall learning and provide a useful experience rather than add unnecessarily to workload.

The first session includes:a personal account by an expert by experience of their illness and recovery;a structured presentation, co-delivered by the psychiatrist and expert by experience, on stigma and its impact on people with mental health problems;one or two video clips of a service user testimony. Some examples of video clips with different styles have been sent to participating sites, so that sites can then find and use appropriate clips, allowing for differences in culture and language;Two role plays by the students, one of each of experienced and anticipated discrimination;At the end of the first session students are provided with an assignment: to describe specific situations they encounter during their psychiatric rotations of anticipated or experienced discrimination reported by service users. The descriptions will then be discussed and reflected upon during the second session.

The second session consists of:Discussion facilitated by both trainers of any experienced or anticipated discrimination students have observed during their time meeting with patients in clinical settings;discussion of how to support healthcare professional colleagues with mental health problems, and possible disclosure of mental illness;how to respond to one’s own mental health problems

### The expert by experience as educator

Where possible service users working as educators or in peer support roles will act as the expert by experience to co-deliver the training. The presentation by the expert by experience will include a description of the onset of illness; current treatment and self-management of illness; examples of stigma and discrimination; and how the illness informs aspects of the person’s life, for example their choice of study or work. The expert by experience can also contribute their views based on the slide content during both sessions, subject to the time available. The service user will be asked to refrain from generalised criticism of health professionals or services as medical students are not responsible for these shortcomings. In addition to decreased anxiety as a result of positive contact, empathy is an important mechanism for stigma reduction [33], and if students are made to feel defensive it will be more difficult for them to empathise with the service user. The psychiatrist and expert by experience will debrief together after each session to discuss what went well and any concerns.

### Control arm

A control arm is important for two reasons. First, to control for any effect of psychiatry training that occurs between the first and second sessions; second, to control for the possible effect of the baseline measures (see below). The control group will therefore be administered all the measures at the same times as the intervention group, i.e. at two sessions during which the intervention group is receiving the training. Alternatively, two separate, consecutive psychiatry rotations may act as the intervention and control groups, if this is feasible. Students will be allocated by the trainer to either the control or the intervention group according to their usual local teaching group allocation at each site.

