### Statistical analysis

Total scores for MAKS, MICA2 and the OSCE will be calculated so that a higher total score represents a more favourable outcome. Descriptive summaries of score changes will be calculated between the baseline and follow up time points for each group. Parametric and non-parametric tests will be employed to detect statistically significant differences in means on individual-level data before and after implementation of the intervention compared to the controls. Statistical analyses of individual-level data will be conducted using a random effects model accounting for clustering within sites and countries, to take into account the between country and culture variation in the attitudes towards mental illness. Changes in each outcome will be investigated at baseline and at the follow up time point after the intervention. All models will be adjusted for gender; age (as a continuous variable); country income category (high, middle or low) and familiarity with people with mental health problems (self or other i.e. family member, friend). In order to appropriately quantify the direct and indirect effects of empathy and anxiety on the three outcomes (MAKS, MICA2 and the OSCE), we will conduct a mediation analysis under the causal framework with the use of the g-computation formula, which has been shown to produce reliable estimates in such scenarios (http://aje.oxfordjournals.org/content/early/2014/12/10/aje.kwu239.full.pdf).

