Another possible limitation of the study is self-selection bias – i.e. students who already have less stigmatising attitudes and behaviour may be more likely to participate in the study, and may wish to be in the intervention group. Sites will therefore assign medical students using existing teaching groups to either the intervention or control group. To encourage control students to still attend and to minimise drop out rates, the OSCE examiner will provide oral feedback at the end of the second OSCE, which students may find useful for their general medical training and their future examinations [29].

The results of this study will help medical schools in high, middle and low income countries to implement manualised training to enable future doctors to reduce the effects of mental illness related discrimination on their patients.

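### No random rule decides which existing teaching group receives READ: the trainer allocates, which leaves the arm comparison open to differential change that the planned adjustment does not address

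*Protocol article*

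**What the plan says.** The Methods/design section is open about the design: "This is a multisite, non-randomised controlled study". The Control arm section gives the allocation rule: "Students will be allocated by the trainer to either the control or the intervention group". The basis is how each site normally forms its teaching groups. The Discussion explains it. Students with less stigmatising attitudes may be keener to take part and may want the intervention, so "Sites will therefore assign medical students using existing teaching groups to either the intervention or control group".

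On timing, the default is concurrent: "The control group will therefore be administered all the measures at the same times as the intervention group". The same section then permits a second arrangement, in which "two separate, consecutive psychiatry rotations may act as the intervention and control groups, if this is feasible". The article states no order for the two rotations.

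On adjustment, the Statistical analysis section says "All models will be adjusted for gender; age (as a continuous variable); country income category (high, middle or low"), and adds familiarity with people with mental health problems. The random effects account for sites and countries. Trainer, teaching group and period are not listed.

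**The concern.** Usual teaching arrangements determine which students sit together. They do not determine which of two groups becomes the READ group. Someone has to decide that, and the protocol names the trainer. The safeguard in the Discussion is aimed at selection by students and leaves selection by the trainer untouched. No chance mechanism or other fixed rule is described in the Abstract, the Control arm section or the Discussion.

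The Control arm section says the control group is there to account for psychiatry teaching received between the two sessions. That works only if both groups would have changed alike without READ. If the choice of group is linked to how the group is taught or where it is placed, the difference between arms mixes the effect of READ with that other change. More students would not remove such a bias.

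**Working it through.** The plan states no figure on this point, so the check is first a reading of the passages and then an illustration under stated assumptions.

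**1. What baseline measurement removes.** For teaching group g, write the baseline mean as μ + a(g) and the follow-up mean as μ + a(g) + c(g) + δ·READ. Here a(g) is the stable level of the group, c(g) its change without READ, and δ the effect of READ. The between-arm difference in change is

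δ + [c(READ group) − c(control group)].

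The a(g) terms cancel and the c(g) terms do not. The risk is therefore differential change, not baseline imbalance as such.

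**2. What the covariates remove.** Country income is constant within a site, so it cannot adjust a contrast between two groups at the same site. Gender, age and familiarity describe students, not the teaching, placement or period of the group. Site and country random effects absorb differences between sites, not between groups within a site.

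**3. Illustration of consequences.** Inputs: 448 per group and 10% dropout (Sample size section), so 448 × 0.9 = 403 analysed per arm; 25 sites; MAKS SD 2.89. Assumed, because the document does not give them: two-sided alpha 0.05; a systematic difference in change of b SD in the same direction at every site; one group per arm per site, m = 403/25 = 16.1 students; teaching-group ICC of 0, 0.01, 0.05 or 0.10.

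SE = √(2 × [ICC + (1 − ICC)/m] / 25). With ICC = 0 this is √(2/403) = 0.070. With ICC = 0.05 it is √(2 × [0.05 + 0.95/16.12] / 25) = 0.093.

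False-positive rate = 1 − Φ(1.96 − b/SE) + Φ(−1.96 − b/SE).

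| b (SD) | MAKS points (b × 2.89) | ICC 0 | ICC 0.01 | ICC 0.05 | ICC 0.10 |
|---|---|---|---|---|---|
| 0.1 | 0.29 | 29% | 26% | 19% | 15% |
| 0.2 | 0.58 | 81% | 75% | 57% | 43% |
| 0.3 | 0.87 | 99% | 98% | 90% | 77% |

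These rates show what would follow if such a bias existed. They are not evidence that it does.

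**4. What a random draw does.** Suppose the two groups at each site differ in change by b, and a draw at each of 25 equally weighted sites decides which one gets READ. The net imbalance then has mean 0 and SD b/√25: 0.02, 0.04 or 0.06 SD for b = 0.1, 0.2 or 0.3. If the choice always favours the same arm, the full b remains. The sample size is unchanged at 448 per group.

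**5. Limit for consecutive rotations.** At a site with one rotation per arm, arm and period coincide whichever comes first. A random order balances period only across sites. It also leaves READ first at some sites, where material can pass to later controls.

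The 448 is used here only as the planned recruitment. How it was derived is a separate matter on which this point does not depend.

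**The case against.** The strongest reply is that the study declares itself non-randomised and says how groups are assigned, so nothing is misstated and the point asks for a different design. The allocation sentence also ties the trainer to the usual teaching groups and can be read as applying an existing structure rather than choosing freely. Both arms have a baseline measurement, and controls are by default measured concurrently. The study is unfunded, runs at 25 sites in 15 countries, acknowledges reduced resources at some of them, and needs an expert by experience to co-deliver.

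Much of this stands and limits the point. Disclosure does not remove the bias, however, and the usual grouping still leaves open which group is READ. A draw between the same intact groups would meet the Discussion's rationale equally well, and the article gives no reason against one.

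A reader might go further in several ways that the document does not support:

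- **Arm is confounded with calendar time throughout.** This applies only at sites using consecutive rotations. That no order is stated does not show that any order is allowed, because the manual is not shown. No timetable shows that controls who go first are less advanced.
- **Trainers will pick the keener group, their own group or the better hospital.** No passage suggests it.
- **The bias is a known share of the target effect.** Differences of 0.1 to 0.2 SD would be 15% to 30% of the stated effect size (0.1/0.66 and 0.2/0.66), but the numerator is only assumed.
- **Randomising costs nothing, or this is the study's largest avoidable weakness.** Scheduling freedom would be lost, and nothing in the document supports such a ranking.

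**Conclusion.** The point holds as a modest, worthwhile design improvement. The allocation rule names the trainer and gives no chance mechanism for which existing group receives READ. The stated safeguard covers self-selection by students only. After baseline measurement the remaining threat is differential change through teaching or placement, and through period where consecutive rotations are used. The listed covariates do not address it.

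Its size cannot be estimated from the document. The false-positive rates above rest on an assumed bias in one direction at all sites, an assumed ICC and an assumed alpha. They show why the matter is worth settling, not how large the bias is.

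**What to change.** In the Control arm section, replace allocation by the trainer with this rule: teaching groups stay intact, and the lead site issues each site a random assignment of its existing concurrent groups to READ or control. Bring the matching sentence in the Discussion into line.

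Where a site uses consecutive rotations, the lead site rather than the trainer sets the order in advance and records it. If that order is drawn at random, state that it balances period only across sites and that leakage to controls remains possible where READ comes first.

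Keep any site that cannot comply, flag it as non-randomised, and repeat the main model in the randomised sites only.

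The cost is a list generated at the lead site and some loss of scheduling freedom for trainers, which matters in an unfunded multi-country study. No additional students or staff are needed.
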